### Data Management

Data will be collected using paper and electronic CRFs, managed by the principal investigator, and stored securely. Participants will be assigned a unique enrollment number. Data entry will prioritize accuracy, and the data will be stored for at least 5 years after study completion.

### Protocol Amendments

The trial is being conducted according to the approved protocol. Any deviation required in the protocol, including changes in the interventions or methods, will be reported to the sponsors and the institutional ethics committee (IEC), along with justification. Protocol amendments will be implemented only after IEC approval, following standard procedures.

### Statistical Methods

The primary outcome of the study, namely, the proportion of participants achieving an improvement in the WAZ of ≥0.5, will be analyzed using an intention-to-treat approach. Between-group comparisons for the primary binary outcome will be performed initially using the chi-square test, followed by multivariate logistic regression to estimate adjusted effect sizes after controlling for important covariates, including study center, baseline, WAZ, age, sex, and other clinically relevant variables. This will be done in the following steps:

Step 1: an unadjusted between-group comparison will be performed using the chi-square test to examine the crude difference in the proportion of participants achieving the primary outcome between the intervention and control groups. This provides transparency and allows readers to evaluate the raw effect.Step 2: multivariate logistic regression will be used to estimate the adjusted odds ratio and 95% CI, while controlling for the following prespecified covariates: study center, baseline WAZ (continuous), age (months), sex, baseline nutritional status category, socioeconomic status, and educational status of parents. The adjusted analysis represents the primary analytic result and will be emphasized in reporting and interpretation.

For the secondary outcomes, within-group pre-post changes will be examined using a paired *t* test or Wilcoxon signed-rank test, as appropriate, and will be reported for descriptive purposes. For parameters assessed at multiple follow-up time points, repeated-measures ANOVA or the Friedman test will be applied to assess temporal trends. All analyses will be performed using SPSS (version 29.0; IBM Corp), and statistical significance will be assessed at α=.05 (2-tailed).

Participants who withdraw, are lost to follow-up, or do not complete the week 12 assessment will be documented, and reasons for dropout will be recorded. Dropout rates and reasons will be presented by study group in the CONSORT (Consolidated Standards of Reporting Trials) flowchart.

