### Outcome Measures

The primary outcome measure is the proportion of participants attaining a change in the weight-for-age *Z* score (WAZ) by ≥0.5, as per WHO reference standards, from baseline to weeks 12 and 16. The secondary outcome measures include changes in anthropometric measurements (weight in kg, height in cm, and midupper arm circumference in cm), which will be assessed every 2 weeks for 12 weeks, followed by assessment at week 16. Change in the frequency of illnesses will be assessed at baseline, week 12, and week 16 using a predesigned table that records the frequency and duration of illnesses. Assessment of safety (complete blood count [CBC], liver function test [LFT], renal function test [RFT], and serum electrolytes) will also be performed at baseline and week 12 in a small proportion of participants whose parents provide consent.

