### Sample Size

The sample size for the study has been calculated assuming that 60% of participants in the intervention arm and 30% of participants in the control arm will achieve a change in *Z* score of ≥0.5 according to the WHO weight-for-age growth standards. With a 95% CI and 80% power, 42 participants per group need to be enrolled in the trial. After accounting for an attrition rate of 20%, the sample size for the study has been finalized as 50 per group. Therefore, a total of 100 participants per center will be enrolled in the trial.

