#### Follow-Up Assessments

All participants will undergo follow-up assessments on days 14, 28, 42, 56, 70, 84, and 112. Concomitant medication, rescue medication, drug compliance, and adverse drug reactions or adverse drug events will be assessed during the follow-up visits. Laboratory investigations will be performed at the day 84 visit for those who underwent baseline laboratory assessments (Table 1).

**Table 1 table1:** Study schedule.

Assessments	Screening or baseline	Follow-up		
		Weeks 2-10 (days 14, 28, 42, 56, and 70)	Week 12 (day 84)	Week 16 (day 112)
Informed consent from parent	✓			
Laboratory investigations (for those who are willing)	✓		✓	
Demographic characteristics and medical history	✓			
Weight-for-age *Z* score	✓		✓	✓
Anthropometric measurements (weight, height, midupper arm circumference, and BMI)	✓	✓	✓	✓
Assessment of illness frequency	✓		✓	✓
*Dosha*, *dhatu*, and *srotopareeksha* assessment	✓			
Assessment of concomitant medications		✓	✓	✓
Assessment of rescue medications		✓	✓	✓
Assessment of adverse drug reactions and adverse events		✓	✓	✓
Drug compliance assessment		✓	✓	
Dispensing of trial drug and compliance reporting form	✓	✓		

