The *Kashyapa Samhita*, a classical textbook of Ayurvedic pediatrics, defines “Lehana” as a formulation that is heavy to digest but nourishing and is recommended for emaciated children [18]. *Ayush-BR Leham*, the trial drug, is one such nutritional supplement. The nutrition supplied after digestion correction is expected to be properly digested and assimilated by the body, supporting healthy weight gain [19]. Studies support that intestinal dysfunction, inflammation, and environmental enteric dysfunction can impair nutrient absorption despite adequate intake from fortified foods [20]. Hence, the sequential treatment approach is conceptually robust, as it aims to optimize digestive and metabolic functions before nutritional supplementation, thereby enhancing nutrient bioavailability and assimilation [21]. Such a strategy is likely to promote more effective and sustained recovery, rather than transient weight gain alone. This study design thus offers more treatment responsiveness and reduces the likelihood of incomplete recovery observed in standard supplementation-based interventions.

This study is designed as an exploratory randomized controlled trial to evaluate the efficacy of the nutritional supplement, *Ayush-BR Leham*, in moderately malnourished children. It is hypothesized that the trial intervention will result in a clinically meaningful improvement in nutritional status, reflected by an increase of ≥0.5 in WAZ among moderately malnourished children. Additionally, the intervention is expected to improve anthropometric parameters and reduce illness frequency compared with the control group.

The study has several strengths, including a randomized controlled design, the use of standardized and clinically relevant outcome measures such as WAZ, and repeated follow-up assessments that enable evaluation of trends over time. WAZ is a well-established indicator of child mortality and is sensitive to changes associated with nutritional interventions. Previous trials have demonstrated that improvements in WAZ reflect meaningful recovery and improved clinical outcomes [22,23]. Even mild improvements in WAZ following a short-term intervention with a nutritional supplement signify a positive shift in overall nutritional status and reduced morbidity. Additionally, a *Z* score ≥0.5 exceeds the normal day-to-day variation expected due to fluctuations in hydration status, illness, or measurement errors [24].

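### The plan states no between-arm estimate of continuous growth: follow-up WAZ is used only as a ≥0.5 responder, and secondary outcomes get only within-group or time-trend tests

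*Protocol article*

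**What the plan says.** **Primary outcome.** Outcome Measures defines it as the proportion of children whose WAZ changes by at least 0.5 "from baseline to weeks 12 and 16". Statistical Methods repeats it as "The primary outcome of the study, namely, the proportion of participants achieving an improvement in the WAZ of ≥0.5". The analysis has two steps: a crude chi-square test, then a logistic regression whose adjusted odds ratio is named as the primary result. Both steps use only the binary outcome. WAZ on its continuous scale enters once, as a baseline covariate.

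**Secondary outcomes.** "The secondary outcome measures include changes in anthropometric measurements (weight in kg, height in cm, and midupper arm circumference in cm") every two weeks to week 12 and again at week 16, with illness frequency and safety laboratory tests. Change in WAZ as a continuous quantity is not listed.

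**Secondary analysis.** Statistical Methods names paired t or Wilcoxon signed-rank tests within each group, reported descriptively, and repeated-measures ANOVA or Friedman tests for trend over time. No group term or group-by-time term is stated.

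**Data collected.** Table 1 (Follow-Up Assessments) has WAZ at baseline, week 12 and week 16, and "Anthropometric measurements (weight, height, midupper arm circumference, and BMI") at every visit.

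**Design figures.** Sample Size assumes "60% of participants in the intervention arm and 30% of participants in the control arm" will respond, and states: "With a 95% CI and 80% power, 42 participants per group need to be enrolled in the trial". Elsewhere, "statistical significance will be assessed at α=.05 (2-tailed").

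**The concern.** The trial randomizes children to two arms and records their growth on a continuous scale, yet the only between-arm comparison of growth that is written down is a comparison of proportions above a cut. The continuous secondary outcomes do not fill the gap. A paired test within one arm does not estimate a treatment effect, and a time trend without a group term does not either (the Friedman test has no place for one).

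This sits badly with two aims in the article's own Discussion. Anticipated Findings expects anthropometry to improve relative to the control group, and no stated analysis tests that. The same section presents the trial as a source of preliminary evidence for larger confirmatory studies. A mean difference in WAZ with its confidence interval is one of the figures such studies would use, and the plan does not produce it.

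At stake is the ability to detect, and to describe precisely, an effect smaller than the one designed for. Anticipated Findings remarks that "Even mild improvements in WAZ following a short-term intervention with a nutritional supplement signify a positive shift in overall nutritional status"; a modest shift of that kind is where a responder analysis is least sensitive.

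**Working it through.** **Inputs from the article.** Response rates 60% and 30%; two-sided 5% level; 80% power; 42 per group; 20% attrition; 1:1 allocation; 200 children in total. Evaluable per arm = (200/2) × (1 − 0.20) = 80.

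**Input assumed.** WAZ change is normal with the same SD in both arms. The article gives neither an SD nor a distribution. Working in SD units, the value of the SD is not needed.

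**1. The plan's own figure.** With p̄ = 0.45, the pooled-variance formula without continuity correction is

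n = [1.960 × √(2 × 0.45 × 0.55) + 0.8416 × √(0.60 × 0.40 + 0.30 × 0.70)]² / (0.60 − 0.30)²
= (1.379 + 0.565)² / 0.09 = 41.97, so 42 per group. The stated figure is reproduced.

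**2. The same effect as a shift in means.** d = z(0.60) − z(0.30) = 0.253 + 0.524 = 0.778 SD.

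n = 2 × (1.960 + 0.8416)² / 0.778² = 25.95, so 26 per group.

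Ratio 26/42 = 0.62. These are normal approximations. Exact calculation gives 41 per group for the chi-square test (the first size to pass 80% power) and 27 for the t test, a ratio of 27/41 = 0.66. The responder test therefore uses roughly 62% to 66% of the information.

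**3. What this means at 80 per arm.** Responder power = Φ{[|p₁ − p₂|√n − 1.960√(2p̄(1 − p̄))] / √(p₁(1 − p₁) + p₂(1 − p₂))}. Power for means = Φ(d√(n/2) − 1.960).

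| True rates | Shift (SD) | Responder test | Comparison of means |
|---|---|---|---|
| 60% vs 30% | 0.778 | 97.4% | 99.8% |
| 50% vs 30% | 0.524 | 74% | 91% |
| 45% vs 30% | 0.399 | 50% | 71% |

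Worked line for 50% vs 30%: responder (0.20 × 8.944 − 1.358)/0.678 = 0.635, Φ = 0.74; means 0.524 × 6.325 − 1.960 = 1.357, Φ = 0.91.

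**4. Smallest shift detectable at 80% power, 80 per arm.** Means: (1.960 + 0.8416) × √(2/80) = 0.443 SD. Responders against a 30% control rate: 51.6%, which is 0.565 SD.

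**5. Sensitivity to the rates.** The ratio of sample sizes (means to responders) is 58/93 = 0.62 at 50% vs 30% and 99/163 = 0.61 at 45% vs 30%. It falls when responders are rare, for example 43/141 = 0.30 at 15% vs 5%. These rates are illustrations, not figures from the article. None of the results counts any gain from baseline adjustment.

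**The case against.** The strongest reply is that the primary endpoint is sound and only an optional extra is being asked for. Much of that stands.

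- **The cut is justified.** A reader might infer from the remark on mild improvements that the 0.5 threshold contradicts the Discussion. It does not. The hypothesis there is framed as a gain of at least 0.5, and the same discussion defends the threshold as lying beyond day-to-day variation and measurement error. Scoring a gain of 0.4 as a non-response is a property of any responder endpoint.
- **The trial is not underpowered for its target.** A reader might infer that from the comparison of 26 with 42. Enrolment is complete, so no children are saved, and at the design rates the responder test has about 97% power with 80 per arm.
- **The information is not lost for good.** WAZ is stored, and weight in kg, given age and sex, carries much of the same signal. The data are available; what is missing is a stated between-arm analysis of either. Weight is to be analysed only within groups or for trend, so as written it does not supply the comparison.
- **A separate analysis plan could add this.** It could. But the article sets out its outcomes and its two-step primary analysis in detail and names the tests for secondary outcomes. The point is directed at what those sections fix, not at detail they leave open.
- **WAZ at every fortnightly visit in a mixed model would be excessive.** Agreed that it is not needed. Both arms receive the same treatment to day 28, so the first two follow-up visits carry no treatment contrast.

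**Conclusion.** The point holds in a limited form. The plan states no between-arm estimate for any continuous growth outcome, and follow-up WAZ is used only through the 0.5 cut. The consequence is weaker precision and power for effects smaller than the design effect: about 17 percentage points of power at 50% versus 30% (74% against 91%) and 21 at 45% versus 30% (50% against 71%), with 80 evaluable per arm. At the design effect the cost is negligible.

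The power figures rest on a normal, equal-SD WAZ change and on attrition of exactly 20%. The finding that no between-arm continuous analysis is stated does not depend on either assumption. The documents do not support the stronger conclusions that the responder primary is wrong or should be replaced. This is a worthwhile improvement to make before analysis, not a flaw that invalidates the trial.

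**What to change.** Keep the responder outcome as primary. Before the data are analysed, prespecify one supportive secondary analysis: the between-arm difference in WAZ at week 12, then at week 16, by ANCOVA adjusted for baseline WAZ, center, age and sex, reported with a 95% CI. Computing WAZ at the fortnightly visits and fitting a mixed model is optional.

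Cost: no new data and one further secondary result to report. Because it changes the methods, it should go through the procedure in Protocol Amendments (justification and ethics committee approval). It should also be labelled openly as added after enrolment was complete in an open-label trial. Fixing it before the data are examined protects it from being read as post hoc.

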**Methods:**

This is a multicenter, open-label, randomized controlled, 2-group pilot study designed to enroll 200 moderately malnourished children, 100 from each participating study center of the Central Council for Research in Ayurvedic Sciences. The children will be screened for moderate malnutrition using the World Health Organization weight-for-age *Z* score through the AnthroCal app developed by the All India Institute of Medical Sciences, New Delhi. After obtaining consent from parents, the participants will be randomized and allocated to 2 groups. The study group will receive *Aravindasava*, 5 mL twice daily after food for 4 weeks, followed by *Ayush BR Leham*, a nutritional supplement, 5 g twice daily before food from weeks 5 to 12. The control group will receive *Aravindasava* for 4 weeks and thereafter receive no intervention for 8 weeks. Both groups will be advised to follow a home-prepared diet during the study period. A follow-up assessment will be conducted after 4 weeks. The primary outcome is a change of ≥0.5 in the World Health Organization weight-for-age *Z* scores, and the secondary outcomes are changes in anthropometric measurements, the frequency of illnesses assessed using a predesigned table, and safety parameters assessed using biochemical measures.

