### Objective

The study’s objective is to evaluate the therapeutic efficacy and safety profile of *Ayush-BR Leham* in children aged 3 to 5 years with moderate malnutrition.

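### The stated analysis of the laboratory safety outcome makes no comparison between arms and is insensitive to a marked abnormality in a few children

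*Protocol article*

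**What the plan says.** The Objective section sets out to "evaluate the therapeutic efficacy and safety profile" of the product, so safety is part of the single stated objective. The Abstract (Methods) names among the secondary outcomes "safety parameters assessed using biochemical measures". Outcome Measures lists blood count, liver and renal function and electrolytes in the same paragraph as the other secondary outcomes, and says that this assessment "will also be performed at baseline and week 12 in a small proportion of participants whose parents provide consent". The size of that subset is not given.

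Statistical Methods then fixes the method: "For the secondary outcomes, within-group pre-post changes will be examined using a paired" t test or a Wilcoxon signed-rank test, and these results "will be reported for descriptive purposes". The next sentence reads: "For parameters assessed at multiple follow-up time points, repeated-measures ANOVA or the Friedman test will be applied to assess temporal trends". The laboratory tests have one follow-up time (week 12, as Table 1 confirms), so that sentence does not reach them. Two-sided significance at 0.05 is set for all analyses. No between-arm comparison is stated for secondary outcomes.

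Safety Monitoring defines a safety population and provides for adverse-event monitoring at every visit. Its listed sources include the laboratory assessments in the subset. Outside the subset, laboratory tests are done when there is a clinical reason.

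**The concern.** Two features of the stated method fit the laboratory outcome badly.

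First, it looks within each arm only. Under Trial Design and Interventions, both arms take *Aravindasava* for 4 weeks, and only the study arm then takes *Ayush-BR Leham* for 8 weeks. A change from baseline to week 12 within the study arm mixes the two products with 12 weeks of growth, diet and intercurrent illness. Only the contrast with the control arm removes what the arms share.

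Second, liver, kidney or blood toxicity can show as a large change in a few children. A paired t or Wilcoxon test asks whether the average or typical child has moved. One very large value raises the standard deviation along with the mean, so the t test can become less likely to reach significance when a child is affected than when none is.

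At stake is the laboratory part of the safety objective. Reported as written, it would consist of p values for average change. These neither show how many children became abnormal nor say how large a risk the small subset leaves open.

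**Working it through.** **The plan's own figure.** The only sample size calculation is for the primary outcome: 60% against 30%, two-sided 0.05, 80% power. With pooled variance, n = [1.960·√(2·0.45·0.55) + 0.842·√(0.24 + 0.21)]² / 0.30² = 41.97, so 42 per group, as stated. It says nothing about the laboratory analysis, for which the protocol gives no figure.

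**Inputs.** Alpha 0.05, two-sided (Statistical Methods). Two time points (Outcome Measures, Table 1). Subset size per arm: not stated; 10 to 50 is assumed below.

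**Step 1: limit of the paired t test.** Let k of n children have the same very large change D, beside which the changes in the others are negligible.

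- Mean change = kD/n.
- Variance of the changes = D²·k(n−k) / [n(n−1)].
- Hence t → √[k(n−1)/(n−k)], whatever the values of D and the background SD.

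| n per arm | 5% critical t | k=1 | k=2 | k=3 | k=4 |
|---|---|---|---|---|---|
| 10 | 2.26 | 1.00 | 1.50 | 1.96 | 2.45 |
| 20 | 2.09 | 1.00 | 1.45 | 1.83 | 2.18 |
| 30 | 2.05 | 1.00 | 1.44 | 1.80 | 2.11 |
| 50 | 2.01 | 1.00 | 1.43 | 1.77 | 2.06 |

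Up to three affected children (30% of 10, 15% of 20, 6% of 50) stay below the critical value. A fourth crosses it.

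**Step 2: finite changes, by simulation.** Assumptions: SD of change 8 units; affected children rise by 160 or 360 units; n = 10, 15, 20, 30 or 50; 4,000 runs for t and 1,000 for Wilcoxon. The table gives the range of the proportion of runs with p < 0.05.

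| Affected children | Paired t | Wilcoxon |
|---|---|---|
| 0 | 4.2–5.3% | 4.0–6.4% |
| 1 | 0–0.1% | 3.7–5.8% |
| 2 | 0–0.8% | 4.5–9.8% |
| 3 | 0–9.9% | 7.5–20.3% |

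With one or two affected children the t test rejects less often than with none. Wilcoxon stays at its false-positive rate with one and rises only modestly with two or three.

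**Step 3: what the tests can find.** For a uniform mean shift of 0.5 SD of the change (assumed), the noncentral t gives miss rates of 71%, 44% and 25% at n = 10, 20 and 30. The shift is therefore detected 29%, 56% and 75% of the time.

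**Step 4: what a count would say.** With zero cases among n children, the one-sided 95% upper limit is 1 − 0.05^(1/n): 25.9%, 13.9% and 9.5% at n = 10, 20 and 30. The upper end of a two-sided exact 95% interval is 1 − 0.025^(1/n): 30.8%, 16.8% and 11.6%.

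**The case against.** The case on the other side has weight on several points.

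- **Individual cases may be found elsewhere.** A reader might infer that the paired test is the only way this trial can notice a child with a marked abnormality. The document does not support that. Safety Monitoring names the subset's laboratory assessments as one route to adverse-event detection, and Table 1 puts adverse-event assessment at the same week 12 visit as the repeat tests. This stands, and it limits the point to the stated laboratory analysis.
- **No claim that a null result proves safety.** A reader might infer that the plan will treat non-significance as proof of safety. It nowhere says so, and it labels these tests descriptive. This stands too. However, a p value for average change is a poor description of laboratory safety under any label.
- **The result is not bound to be null.** A reader might infer that the laboratory results will almost surely be non-significant whether or not children are harmed. Step 3 shows that a common shift can be detected, and Wilcoxon is an allowed alternative. Many parameters would also be tested: if 20 independent tests per arm are assumed, the chance of at least one p < 0.05 with no harm is 1 − 0.95^20 = 64%. So the p values can mislead in either direction.
- **A fuller plan may contain shift tables.** It may, and their absence from a journal article is no fault. The point is that the article states a method for secondary outcomes, counts laboratory safety among them, and the method suits that outcome poorly. Statistical Methods does not mention laboratory data by name, so the link runs through the Abstract and Outcome Measures.
- **The real limit is the small subset.** True. Better reporting does not enlarge it; it only makes the remaining uncertainty visible.

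**Conclusion.** The point holds for the stated analysis of the laboratory outcome, not for all the safety evidence in the trial. The one stated method that fits these data compares no arms, although the arms share the first product. In the t-test limit it also stays non-significant with up to three markedly affected children among 10 to 50 tested per arm.

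The limiting t result is algebra: it needs an equal, very large change in the affected children, but no particular SD or size of rise. The simulated rates, the 0.5 SD shift and the zero-case limits rest on assumed values, above all the subset size, which the protocol does not state. If 10 to 30 per arm are tested, zero cases would still be compatible with a true rate of up to about 26% to 9.5% (one-sided 95%). The change is worth making because it replaces a poorly suited stated method with a better one on the same data.

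**What to change.** In Statistical Methods, take the laboratory parameters out of the sentence on paired tests and add text to this effect:

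> For each laboratory parameter, a shift table by arm will classify baseline and week 12 values against age-specific reference ranges. The number of children tested, and the number and proportion who move outside the range or who worsen from an already abnormal baseline, will be given with exact (Clopper-Pearson) 95% confidence intervals. Every such child will be listed. The between-arm difference in mean change will be given with its 95% confidence interval. A non-significant change will not be read as evidence of safety.

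Worsening from an abnormal baseline needs a definition, set before the laboratory data are examined.

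Cost: revised wording and one table per parameter, from data already collected, with no extra samples, visits or children. Under Protocol Amendments, the change would go to the sponsor and the ethics committee. The Results section places data analysis still ahead, so there is time. The downside is a less favourable safety statement, because the wide upper limits from a small subset become visible.

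### No between-arm comparison is named for weight, height, arm circumference or illness frequency, although benefit over control is expected on each

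*Protocol article*

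**What the plan says.** Outcome Measures lists the secondary efficacy outcomes. "The secondary outcome measures include changes in anthropometric measurements", namely weight, height and midupper arm circumference, taken every 2 weeks to week 12 and again at week 16. "Change in the frequency of illnesses will be assessed at baseline, week 12, and week 16".

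Statistical Methods assigns the comparison of arms to one endpoint: "Between-group comparisons for the primary binary outcome will be performed initially using the chi-square test", followed by an adjusted logistic regression that is the emphasised result. For the other outcomes it reads: "For the secondary outcomes, within-group pre-post changes will be examined using a paired" t test or a Wilcoxon signed-rank test, and these "will be reported for descriptive purposes". For parameters measured repeatedly, "repeated-measures ANOVA or the Friedman test will be applied to assess temporal trends". The section closes with a two-sided significance level of 0.05 and does not exempt the within-group tests from it.

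The Discussion (Anticipated Findings) words the expectation comparatively: "the intervention is expected to improve anthropometric parameters and reduce illness frequency compared with the control group".

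**The concern.** The question asked of the secondary outcomes is comparative, but the methods named for them are not stated to compare the arms. A change from baseline within one arm contains everything that happens to these children over 12 to 16 weeks. That includes ordinary growth at age 3 to 5 years. It also includes the Aravindasava phase, dietary counselling and management of infections, all of which Interventions gives to both arms. For illness frequency, Baseline Assessments takes the starting value from the 3 months before enrolment, so a before-after contrast can also mix recall and season with treatment. Only the concurrent control arm separates these from the effect of the supplement.

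If the section is followed as written, the secondary results would not use the randomisation. Two readings would then be open, and neither is sound: that a significant rise in the study arm shows benefit, or that significance in one arm and not the other shows a difference between them.

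**Working it through.** **1. The plan's own figure.** The only sample-size calculation is for the primary outcome: 60% versus 30%, two-sided 0.05, 80% power. With pooled variance and no continuity correction,

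n = [1.960·√(2·0.45·0.55) + 0.842·√(0.6·0.4 + 0.3·0.7)]² / 0.30² = (1.379 + 0.565)² / 0.09 ≈ 42 per group.

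The stated 42 is reproduced. The present point does not depend on it.

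**2. Method against question.**

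- *Paired t or Wilcoxon signed-rank:* within one arm by definition, so no comparison of arms.
- *Repeated-measures ANOVA:* could carry a group factor and a group-by-time term. The text states neither and gives temporal trends as the purpose.
- *Friedman:* ranks repeated values within each child. It has no place for a factor that separates independent arms, so on this branch no comparison is possible.
- *Chi-square and logistic regression:* these compare arms, but are assigned to the primary binary outcome only.

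No named method is therefore stated to estimate an arm difference for continuous weight, height, midupper arm circumference or illness frequency.

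**3. Illustration of what within-arm tests can show.** The protocol gives no SDs, so the inputs are assumptions: both arms change equally (no treatment effect) by d SDs of the change score, with d from 0.2 to 0.5. Arm sizes are 100 (200 children allocated 1:1) and 50 (one center, from Sample Size).

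Chance that one arm is significant (normal approximation): p = Φ(d√n − 1.96) + Φ(−d√n − 1.96).
Chance that exactly one of the two arms is significant: 2p(1 − p).

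Example, d = 0.2 and n = 100: d√n = 2.0, p = Φ(0.04) + Φ(−3.96) = 0.516, and 2 × 0.516 × 0.484 = 0.499.

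| d | n = 100: study arm significant | n = 100: exactly one arm | n = 50: study arm significant | n = 50: exactly one arm |
|---|---|---|---|---|
| 0.2 | 51.6% | 49.9% | 29.3% | 41.4% |
| 0.3 | 85.1% | 25.4% | 56.4% | 49.2% |
| 0.4 | 97.9% | 4.0% | 80.7% | 31.1% |
| 0.5 | 99.9% | 0.2% | 94.2% | 10.8% |

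The two kinds of error trade places. With a modest shared change, discordant arms are common. With a large one, discordance almost disappears because both arms are significant. Neither pattern says anything about the supplement.

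**4. What a direct comparison offers.** A between-arm test holds the false-positive rate at 5%. Its detectable standardised difference at 80% power is (1.960 + 0.842)·√(2/n): 0.40 with 100 per arm, 0.44 with 80 per arm (after the 20% attrition in Sample Size), and 0.56 with 50 per arm.

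**The case against.** The strongest reply has four parts.

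- *The pre-post tests are labelled descriptive.* This is true and it matters: the protocol does not claim that they establish efficacy, and one should not assume that its authors will use them so. The label does not supply the missing comparison.
- *Repeated-measures ANOVA may include group.* This also stands. A reader might infer that the secondary expectation can never be tested under this plan. The text does not support that: only the pre-post sentence is restricted to within-group changes, and ANOVA could carry the group term. What can be said is that no between-arm comparison is named and that the Friedman alternative could not provide one.
- *An article condenses, and an unseen analysis plan may hold the rest.* That would answer a mere silence. Here the section selects the secondary methods and states their purpose, beside a detailed two-step comparison of arms for the primary outcome. The issue is the choice as fixed, not missing detail.
- *This is a pilot.* The article calls the trial exploratory, and its explicit hypothesis concerns the weight-for-age response. The secondary outcomes are only expected to improve, and that statement sits in the Discussion. This lowers the severity. The expectation is still worded against the control group, and preliminary evidence for a larger trial needs an arm difference with its uncertainty.

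**Conclusion.** The point holds in limited form and should be fixed before analysis. For the four secondary efficacy measures the plan names no comparison of arms, while the article expects an advantage over control on them. Within-arm changes cannot show that advantage.

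A reader might infer that growth as a whole goes uncompared or that the main result is compromised. Neither follows. The weight-for-age response is compared between arms by chi-square test and adjusted logistic regression, and neither that analysis nor its sample size is touched. The gap covers weight as a continuous measure, height, midupper arm circumference and illness frequency.

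The percentages are illustrative only. They rest on assumed equal changes of 0.2 to 0.5 SD, complete data and a normal approximation, and they are not forecasts for any one outcome. The textual finding does not depend on them.

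**What to change.** State a between-arm analysis for each secondary efficacy outcome:

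- **Weight, height, midupper arm circumference:** a linear mixed model with arm, visit, arm-by-visit, baseline value and center, reporting the adjusted arm difference with 95% CI at weeks 12 and 16. Baseline-adjusted ANCOVA at those two visits would also close the gap.
- **Illness frequency:** a count or rate model by arm, adjusted for the baseline count, reporting the between-arm ratio with 95% CI.
- **Within-arm changes:** keep as summary statistics without p-values.

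The cost is a few sentences of analysis text. The measurements are already scheduled and SPSS can fit these models. The article reports enrolment complete with analysis still to come, so the change can go through the route in Protocol Amendments and be dated before the data are analysed.
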